### Study design

The study is a convergent parallel mixed-methods, single-arm repeated measures pilot trial design.

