### Recruitment and screening

Potential participants are recruited via social media and from maternity clinics, shared care General Practitioners and obstetrician clinics around the massage therapists’ locations within Australia. Maternity services and clinics approached are based on the proximity of services to the locations of the massage therapists participating in the study. Potential participants are informed about the study via their obstetric healthcare provider or via social media platforms for stillbirth support services such as SANDS (37) and Red Nose (38). Potential participants contact the researchers via the shared contact information who explain the study and screen potential participants for eligibility (see 2.4.1 and Table 1). Potential participants are given a clear explanation of the requirements of the study, the opportunity to ask questions and time to consider their participation. Individuals who agree to take part must sign an informed consent form. Consenting individuals meeting the criteria of the study are then enrolled in the study.

**Table 1 Tab1:** Inclusion and exclusion criteria

Inclusion criteria
● Pregnant individuals 18 years of age or greater who have experienced a stillbirth or termination for medical reasons (TFMR) from 20 weeks of gestation in a previous pregnancy
● Participants must be less than 30 weeks of gestation
● Participants must be able to attend intervention visits at one of the study pregnancy massage therapists’ clinics located within Australia
● Be able to complete the intervention visits within in a 4-month period
Non-inclusion criteria
● Potential participants will be excluded if their schedule will not allow them to receive the study treatments in the allocated time frame

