### Eligibility criteria

A purposeful sample of pregnant women are being recruited for the HOPES study who have experienced a stillbirth or termination for medical reasons (TFMR) after 20 weeks of gestation in a previous pregnancy (see Table 1). To be eligible to participate, pregnant women need to be less than 30 weeks of gestation. There are no criteria for eligibility related to the interpregnancy interval between the stillbirth and the current pregnancy because evidence shows the impact of stillbirth can be felt for years, and sometimes decades, after the loss (8, 39–41). The mental health of participants experiencing pregnancy after a stillbirth is varied, and we chose not to limit access to the study based on only one or two of the many mental health symptom participants may experience (e.g., anxiety, stress); especially as the mental health of participants is expected to be impacted at different time points during the pregnancy and be unique to each individual and situation (39).

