### Delivery of the intervention

The massages will be provided by a team of massage therapists with experience in pregnancy massage and perinatal loss across multiple sites within Australia. Massage therapists will be recruited (1) through the study personnel who have previously worked with the therapists and or (2) through an expression of interest via a pregnancy massage training organisation in Australia. Therapists from all states and territories across Australia who had completed pregnancy massage training post-completion of their initial massage qualifications are able to express an interest in being study massage therapists. At least 20 massage therapists will be recruited to ensure that there are therapists in differing states and territories across Australia due to the difficulty of recruiting 75 people from a more limited geographic area. The exact number of therapists to be recruited is unknown as it is undetermined how many therapists will express an interest. The massage therapists attend an online 3-h training on the massage study intervention and facilitation of the massage experience for individuals pregnant after a loss as well as training on grief and resources available to individuals pregnant after a loss prior to becoming study massage therapists. The massage treatments are administered in the massage clinician’s office and follow a protocol that allows for treatment to be tailored for each participant depending on the presentation on the day. See Additional file 1 for massage protocol. The focus of each treatment is determined by the participant via the Measure Yourself Concerns and Wellbeing (MYCaW) patient-reported outcome measure (PROM) (46), and the massage therapist administers remedial and or relaxation massage techniques.

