## Data analysis

### Analysis of quantitative data

The participant’s demographic and clinical characteristics will be summarised using descriptive statistics. Summary statistics of the observational clinical treatment data (e.g. worry, anxiety, etc.) will be reported and an appropriate matched test will be used to determine significant differences between baseline and post-final treatment scores (e.g. paired *t*-test if data are normally distributed, Wilcoxon matched-pairs test if not).

Three treatment effect modifiers have been identified: (1) the amount of other support services utilised, (2) passing the gestational age during the study intervention that they experienced their stillbirth, (3) the time between the stillbirth and this pregnancy, and (4) the number of study intervention treatments received. The correlational analysis will be used to determine associations between observational treatment outcomes and support services utilized (e.g. talk therapy (psychology/counselling), peer support etc.). Appropriate comparative tests will be used to determine whether there is a relationship between observed treatment outcomes and gestation of stillbirth, the duration of the interpregnancy interval, and the number of treatments administered.

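### The plain correlation of other support use with outcome can be confounded by baseline severity, and in a single arm it cannot show effect modification

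*Protocol article*

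**What the plan says.** The section Analysis of quantitative data introduces its list of modifiers with "Three treatment effect modifiers have been identified: (1) the amount of other support services utilised". For that item it then prescribes: "The correlational analysis will be used to determine associations between observational treatment outcomes and support services utilized". Talk therapy and peer support are given as examples. No adjustment for the baseline score is mentioned. The text also does not say whether the outcome is the post-treatment score or the change from baseline.

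For the outcomes themselves the same section says that "an appropriate matched test will be used to determine significant differences between baseline and post-final treatment scores", with a paired t-test or a Wilcoxon test as examples. The Study design section describes a "single-arm repeated measures pilot trial design", so there is no comparison group. On who may enter, the Eligibility criteria section says "we chose not to limit access to the study based on only one or two of the many mental health symptom participants may experience". Baseline severity can therefore vary widely. Table 2 shows that anxiety, worry, stress and self-management are measured at enrolment.

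**The concern.** How much other support a woman uses is her own choice, and the article does not tie it to a time before the intervention. If women who are more anxious at entry tend to use more counselling or peer support, support use carries information about baseline severity. Severity also predicts the later score and, through regression to the mean, the change. A plain correlation of support use with outcome then picks up severity even when support does nothing.

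The second problem is the label. To say that support modifies the effect of massage, one must compare the effect of massage between women with more and less support, and that needs an estimate of what would have happened without massage in each group. A single arm has none. The correlation mixes baseline severity, any effect of support itself and any true modification, and it cannot separate them.

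At stake is a secondary result that could say that counselling or peer support helps or harms when it does neither, or that massage works better or worse alongside it. Such a result could be carried into the larger effectiveness trial that this study is meant to prepare.

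**Working it through.** The article gives no figure to reproduce here, so this is a check of what the planned analysis returns when the truth is known.

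**Inputs**
- From the article: 75 women, 10-15% drop-out and 10% incomplete data (Sample size). This leaves 75 × 0.75 = 56.25 to 75 × 0.90 × 0.90 = 60.75, or about 56 to 61 analysable women.
- Assumed, because the article gives neither: a = correlation of support use with baseline severity, range 0.2-0.5; r = correlation of pre and post scores, range 0.5-0.7. Pre and post standard deviations are taken as equal.
- Truth in the check: other support has no effect on the outcome. Higher scores mean worse symptoms, as for the anxiety, worry and stress scales. For the self-efficacy scale, where higher is better, the signs read the other way.

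**Formulas** (standardised scores, support linked to the post score only through baseline severity)
- Correlation of support with the post score: a × r.
- Correlation of support with change: (a·r − a) / √(2(1 − r)) = −a × √((1 − r)/2).
- Partial correlation of support with the post score given baseline: its numerator is a·r − a·r = 0.

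**Central illustration, a = 0.4 and r = 0.6**
- Post score: 0.4 × 0.6 = +0.24, so support looks harmful.
- Change: −0.4 × √(0.4/2) = −0.4 × 0.447 = −0.18, so support looks helpful.
- Chance of a nominally significant result at n = 60, by Fisher's z with √57 = 7.55. Post score: 0.245 × 7.55 = 1.85, and P(Z > 1.96 − 1.85) is about 46%. Change: 0.181 × 7.55 = 1.37, and P(Z > 1.96 − 1.37) is about 28%. A simulation of 20,000 trials gave 46.3% and 27.6%, and 4.8% after adjustment for baseline.

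**Range**

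| a | r | Post score: a·r | Change: −a√((1−r)/2) | Rejection at n = 56, post / change / baseline-adjusted |
|---|---|---|---|---|
| 0.2 | 0.5 | +0.10 | −0.10 | 11% / 11% / 5% |
| 0.2 | 0.7 | +0.14 | −0.08 | 18% / 9% / 5% |
| 0.5 | 0.5 | +0.25 | −0.25 | 47% / 47% / 5% |
| 0.5 | 0.7 | +0.35 | −0.19 | 77% / 30% / 5% |

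The rejection rates in the table come from 8,000 simulated trials per row.

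**Limit of the adjustment.** The clean result after adjustment arises because baseline severity is the only confounder in this model. If women also take up support because they worsen during the study, adjustment is not enough. With a baseline link of 0.3, a pre-post correlation of 0.6 and an assumed link of 0.2 to 0.5 between worsening and uptake, the partial correlation given baseline is still +0.21 to +0.53 with no true effect.

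**The case against.** The strongest reply is that this is a condensed article about a feasibility trial. It speaks only of associations, a correlational analysis may be partial, and the covariates and choice of score may be fixed in an analysis plan that is not shown. The measures are secondary, and the four progression criteria concern recruitment, retention, perceived support and qualitative feasibility. Most of this stands, and it limits the weight of the point. It does not remove it, because the article itself fixes both the method (a correlation) and the label (effect modifier), and the label is wrong for one arm whatever the covariates.

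Several stronger readings are tempting and are not supported:

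- **That the correlation is biased.** The article nowhere says that more distressed women use more support. It can be biased, and the size depends on that assumed link.
- **That therapists steer women to services.** Therapists receive "training on grief and resources available to individuals pregnant after a loss". Referral, or greater uptake because of it, is not described.
- **That concurrent support is a distinct flaw of the paired test.** Concurrent support does stay inside the pre-post change. If 25-75% of women gained 0.2-0.5 SD from it (assumed), the change would be 0.25 × 0.2 = 0.05 to 0.75 × 0.5 = 0.375 SD with inert massage. But this follows from having no comparison group, which the Discussion acknowledges. It calls for a sentence of interpretation, and no reanalysis would cure it.
- **That massage received outside the study goes uncounted.** The questionnaires are not shown and the list of support services is open-ended, so this cannot be verified.
- **That change should be reported only in women whose other support did not alter.** This would select on behaviour after enrolment, which may itself follow from severity, and so could add bias.

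**Conclusion.** The point holds in a limited form. The planned correlation has no stated baseline term and can mislead in either direction. With inert support, a severity-support link of 0.2-0.5 and a pre-post correlation of 0.5-0.7, it is +0.10 to +0.35 with the post score and -0.08 to -0.25 with change. All of this rests on assumed links, not on figures in the article. Independently of any assumption about severity, a correlation within one arm cannot establish that support modifies the effect of massage. The consequence is confined to secondary, exploratory findings, and no go/no-go decision of the trial depends on it. The correction is still worth making, because the baseline scores that it needs are already being collected.

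**What to change.** 1. Replace the plain correlation with a regression of the post score on support use, adjusted for the baseline score of the same measure (or the equivalent partial correlation).
2. Report the result as a descriptive association with its confidence interval, and remove the effect-modifier label from this analysis.
3. Where feasible, record support held at enrolment separately from support started during the study, so that the two are not merged into one amount.
4. State with the results that the pre-post change reflects massage, concurrent support and the passage of time together.
5. State that adjustment for baseline does not remove bias from support sought because of worsening during the study.

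The cost is one changed analysis and a few questionnaire items. The items add slight burden, and women already enrolled would have to recall the support that they had at entry.

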**Methods:**

HOPES will use a convergent parallel mixed-methods, single-arm repeated measures trial design in trained massage therapists’ private clinics across Australia. HOPES aims to recruit 75 individuals pregnant after a previous stillbirth. The intervention is massage therapy treatments, and participants will receive up to five massages within a 4-month period at intervals of their choosing. Primary quantitative outcomes are the feasibility and acceptability of the massage intervention. Secondary outcomes include determining the optimal timing of massage therapy delivery and the collection of measures for anxiety, worry, stress and self-management. A thematic analysis of women’s experiences undertaking the intervention will also be conducted. A narrative and joint display approach to integrate mixed-methods data is planned.

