### Criteria for discontinuing the intervention

The intervention will cease if participants are advised by their obstetric healthcare providers (i.e. on bed rest), if they are no longer pregnant or if the study participant delivers their baby prior to completing the allocated study intervention.

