#### Treatment utilisation

This data will describe when study participants utilised their massages (massage timing) to inform hypothesis generation regarding dosing value.

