#### Data collection

Some women may give birth before receiving their allocated treatments. Intervention delivery and data collection will cease for participants who give birth prior to completing the full study protocol, and collected data will be kept within the data set. Attempts will be made to collect the final quantitative and qualitative data from participants who fall into this category. The inclusion criteria for participants to be no more than 30 weeks of gestation (Table 1) are in place to minimise participants giving birth prior to completing the full study protocol. Participants who give birth prior to completing the full study protocol will be emailed inviting them to complete the post-intervention online questionnaires and informing them that they are able to participate in the in-depth interview (if applicable) if they desire. A follow-up email will be sent 2 weeks after the first email.

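### The number of massages received is labelled a treatment effect modifier and tested against outcome, but in this single-arm trial it is dose received, set after baseline by factors that may also bear on outcome.

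*Protocol article*

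**What the plan says.** The protocol article, under Analysis of quantitative data, announces three treatment effect modifiers and then lists four. The last is "4) the number of study intervention treatments received". The same paragraph continues: "Appropriate comparative tests will be used to determine whether there is a relationship between observed treatment outcomes" and, among other variables, "the duration of the interpregnancy interval, and the number of treatments administered". No test is named and no covariate is mentioned.

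The dose is not assigned. The abstract says "participants will receive up to five massages within a 4-month period at intervals of their choosing", and the Intervention section makes the spacing a joint decision of participant and therapist. Table 1 admits women at any gestation below 30 weeks. Under Criteria for discontinuing the intervention, treatment stops on obstetric advice, or "if they are no longer pregnant or if the study participant delivers their baby prior to completing the allocated study intervention". The Data collection section links the entry limit to completing the course: "The inclusion criteria for participants to be no more than 30 weeks of gestation (Table 1) are in place to minimise participants giving birth" before the protocol is finished. Women who do give birth first are emailed an invitation to complete the final questionnaires.

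**The concern.** An effect modifier is a characteristic across whose levels the effect of treatment differs. Here everyone is treated, there is no comparison group, and the number of massages is the treatment itself, counted at the end. Relating it to outcome is an observational dose-response analysis. Whatever decides how many massages a woman has, and also bears on her anxiety, worry or stress scores, will show up in the result as if it were an effect of dose.

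At stake is the reading of that result. Timing of therapy is a stated objective, and the Treatment utilisation section says that the timing data serve "to inform hypothesis generation regarding dosing value". A dose-outcome association that reflects late entry, obstetric complications or early birth would point that hypothesis in the wrong direction.

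**Working it through.** The plan gives no figure for this analysis (no alpha, effect or power), so there is nothing to reproduce. The check has three steps.

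**1. Does gestation at entry limit the dose?**
- Four months = 4 × 365.25 / 12 / 7 = 17.4 weeks.
- Latest entry that leaves the whole period before birth: 40 − 17.4 = 22.6 weeks if birth is at 40 weeks; 37 − 17.4 = 19.6 weeks if at 37.
- Entry at 29+6 (29.86 weeks) leaves 40 − 29.86 = 10.1 weeks, or 37 − 29.86 = 7.1 weeks.
- Five visits have four gaps. They still fit after entry at 29+6 if the gaps are no longer than 10.1 / 4 = 2.5 weeks, or 7.1 / 4 = 1.8 weeks.

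Time available thus shrinks with later entry across the eligible range. A late entrant can still have five massages, but only at closer spacing.

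**2. Do the same factors bear on outcome?**
- Gestation: the Eligibility criteria section expects mental health to be affected at different points in the pregnancy. The discussion of the questionnaires says that psychological states vary as milestones are passed.
- Birth before completion: this lowers the dose and also moves the final measurement to after birth, on instruments that include a pregnancy worry score and a prenatal coping inventory.
- Obstetric advice to stop: this lowers the dose. That the underlying complication also raises anxiety is plausible, but the document does not say so.
- Choice: women who wanted fewer sessions may differ in need or in satisfaction. The direction is unknown.

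**3. How large could the false signal be?** In these simulations massage has zero effect and the number of massages is related to outcome by a two-sided Spearman test at 5%. The test and every distribution are assumptions.

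*60 women; entry uniform over 12–30 weeks; birth mean 38.5, SD 1.8 weeks; chosen gap 1 to 4.35 weeks.* The two figures come from two ways of modelling choice.

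| Drift in outcome per week of entry gestation | Rejection rate |
|---|---|
| 0.03 SD | 8.0% to 8.6% |
| 0.05 SD | 13.4% to 15% |

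With no drift, the rate was 4.9%.

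*Second set: birth mean 38, SD 2 weeks; chosen gap about 3.5 weeks.* Outcome shifts by 0.3 SD per SD of entry gestation (5.2 weeks), which is 0.3 / 5.2 = 0.058 SD per week. The test rejects in 19% of trials at n = 50 and 27% at n = 75, against about 5% with no confounding. A larger sample makes the false association more frequent.

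**The case against.** The strongest reply is that this is an exploratory analysis in a feasibility trial. The text speaks of observational outcomes and of a relationship, not of causation. The Treatment utilisation section says hypothesis generation, and no progression criterion uses a dose-outcome result. All of that stands, and it limits the weight of the point.

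It is also fair that naming appropriate tests does not rule out covariates, and that an analysis plan not shown may add them. The point therefore rests on the stated label and the stated test, not on missing detail.

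The sizes are open to attack too. A drift of 0.05 SD per week is 0.05 × 18 = 0.9 SD across the assumed 12–30 week entry range, and nothing in the protocol supports so large a figure. This objection stands.

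Two stronger readings are tempting and should be resisted:
- A reader might infer that the 30-week limit contradicts the 4-month period. It does not. Four months is a maximum; Table 1 asks only "Be able to complete the intervention visits within in a 4-month period"; five visits fit after the latest permitted entry; and the Data collection section openly allows for early birth. There is nothing to reconcile.
- A reader might infer that the dose in a later trial would rest on this test. The document does not say so. The remark on dosing value concerns when massages were used, and it is framed as hypothesis generation.

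What the objection does not rescue is the label. Calling the count of massages an effect modifier invites a reading that a single-arm comparison of self-selected doses cannot support.

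**Conclusion.** The point holds in limited form. The number of massages is dose received, settled after baseline by gestation at entry, by birth or obstetric stop, and by choice. Listing it as an effect modifier is wrong, and a bare test of it against outcome, followed as written, is confounded. The direction of this argument needs only the protocol's own rules and its expectation that mental state varies through pregnancy.

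The size is unknown. The range of about 8% to 15% false positives at a nominal 5% illustrates a drift of 0.03 to 0.05 SD per week under assumed entry, birth and spacing distributions. It is not an estimate for this trial. The primary feasibility and acceptability conclusions are untouched. The change is worth making because it is cheap and corrects a stated error.

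**What to change.** - Remove item 4 from the effect-modifier list and call it dose received. The list then has the three items that its introduction announces.
- Report dose by gestation at entry and by the time each woman had before birth or obstetric stop, with the reason for fewer than five massages where known.
- If a dose-outcome estimate is kept, adjust it for gestation at entry and baseline score, and show whether the final measure was taken after birth. Label it descriptive and not evidence of dose-response.

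The cost is mainly wording. Massage dates and baseline scores are already collected, and gestation is known from screening. The reason for a short course may need one extra field, unless the post-intervention questionnaire already records it (its text is in an additional file not shown). The price is a weaker statement about dosing. Adjustment will reduce the confounding but not remove it.
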